**Protocol Appendix**

**Survey Versions**

1. Expert survey 1
   1. Studies 15, 21, & 44
2. Expert survey 2
   1. Studies, 19, 29, & 39
3. Expert survey 1, incentive pilot:
   1. Studies 15, 21, & 44
   2. included option to list email for us to send C$20 Amazon gift card or donate $20 to Canadian Cancer Society
4. Expert survey 2, incentive pilot:
   1. Studies, 19, 29, & 39
   2. included option to list email for us to send C$20 Amazon gift card or donate $20 to Canadian Cancer Society
5. Novice survey 1
   1. Studies 15, 21, & 44
   2. Exclude: Editor question
   3. Include:
      1. Cancer class or lab semesters question
      2. Add email to obtain results

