| SAMPLING  Study sampling and sample sizes:  Our study sampling frame will consist of all (approximately 35) studies being tested in the Reproducibility Project:Cancer Biology. We will categorize the studies based on theoretical and practical features. We will remove studies due to lack of feasibility (e.g. if there is not a clear relevant effect to predict, such as many in vitro studies especially those focused on cell signaling; if maturation date is too far in the future). We will prioritize studies whose results will be published sooner.  We will work with an independent expert to create or edit two to three questions for each study that can be rendered into dichotomized forecasts. In stage 1, participants will forecast all of the first six (all based on mouse models) studies from the cancer reproducibility project plans to publish. Participants will answer two binary elicitations for six events and simplified continuous elicitations for two events.  When mouse survival or tumor growth curves are used, questions will be created around them. When there are no mouse studies, we will shape a question around a study with a quantitative outcome. We plan to conduct a brief pilot to ensure the question types are relatively intuitive. Question formats might vary slightly depending on pilot results.  For the binary elicitation, our questions will take the two^[[2]](#footnote-2)^ of the following general forms:   1. How likely is it that the replication also be significant (at p ≤ .05)? 2. How likely is it that the effect size of the replication will be as large or larger than the original effect size?   For the simplified continuous elicitation (SCE) for the effect size of the specified treatment group, we will use a four question format, based on [9]:  1. What is the lowest effect size you realistically anticipate will be reported for study X?  2. What is the highest effect size you realistically anticipate will be reported for study X?  3. What is your best guess of the effect size you realistically anticipate will be reported for study X?  4. How confident are you (from 0% to 100%) that your estimated interval (lowest to highest) will include the reported effect size from study X?  Investigator sampling and planned strata:  All respondents will be at least 18 years old and will complete an informed consent.  Our primary sample will include two strata:  *a) Independent Experts*: we will create a sample of about 50 to 100 eligible independent international experts by compiling a list of authors from two searchers based on each original study undergoing replication: a) *related article* searches on PubMed and b) articles citing the original report. We will include corresponding authors and anyone who appears at least three times in any single search.  b) Novices: we will recruit a sample of about 50 to 100 medical undergraduate or upper level undergraduate biology majors, graduate students, or postdoctoral fellows at various universities via department mailing lists to participate in our study.  We will aim to include two secondary strata^[[3]](#footnote-3)^:  *c) Originators*: we will contact each co-author on each original research publication for an elicitation.  *d) Replicators*: we will contact each co-author on each replication protocol - only in cases where data collection has not yet been initiated.  Subjects will be approached through email (except non-experts, who may be approached in a class), and administered the questionnaire electronically.  Individuals will be approached up to five times before declaring them as having declined participation.  Sample size:  Our target sample size is as follows:  We will collect forecasts on 3 events in a half hour. We will collect 2 binary forecasts on 6 effects from 6 experiments + simplified continuous forecasts on overall replication rates). We will split the trial sample into two surveys to minimize the number of trials for which participants only have general expertise.  We will target 30 forecasts per participant on 6 events.  We will aim for 150 participants (50X2=100 independent experts + 50 novices) and expect a minimum of 90 (30X2=60 independent experts + 30 novices). |

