| INTERVIEW AND DATA COLLECTION  Interviews will be conducted in 2 stages:   1. Intake interview: in one 30-minute survey presented over the internet (or in person, or by paper and pencil), we will present subjects with a one-page summary sheet describing each replication study (see Appendix 2), as well as a questionnaire (see Appendix 3). Individuals will be approached using appropriate elicitation technique, whereby we first a) describe the goals of the project and how to complete the questionnaire; b) attempt to motivate good performance by explaining how scoring works; c) provide a simple warm up question (asking for a weather forecast); d) elicit replication forecasts; and e) collect additional cognitive and attitudinal measures. The questionnaire will first collect forecasts, then individual difference variables (as applicable), then demographic variables. 2. Forecasts: subjective probabilities on target experiments.    - 1. 2 binary: Significant difference and direction on 3 replication studies      2. 2 @ 4 parameter simplified continuous (best estimate, range, confidence) on overall replication rates.    1. Individual difference variables       1. Actively Open-Minded Thinking[10]       2. Pace of progress of medical research (AKA Medical Boomster-Doomster, adapted from [11])       3. Self-report of expertise for each study       4. Confidence rating of each forecast       5. Time for forecasts       6. Evidence reliance       7. Familiarity with and Anticipated Impact of Reproducibility Project       8. Estimate of perfect replication of effect sizes    2. Demographics:       1. age       2. gender       3. expertise: H index, title/rank (associate professor, full professor, etc.), number of publications, number of citations (all collected from both SCOPUS & Web of Science), nationality/region 3. Post-event Interview: Once results are available, all participants will be approached for posterior and recalled forecasts. We will collect the first set of posterior distributions when the first batch of results is published. Once all data are collected, we participants will be debriefed about study hypotheses and offered an opportunity to learn their forecast skill against the average of their peers. |

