| SECONDARY ANALYSIS ON FORECAST SKILL^[[4]](#footnote-4)^  An a priori power analysis suggests we need a sample size of 34 per group to detect if detect if the experts differ from (d = .5) the novice group assuming power = .80 and alpha = .05, and we need about 180 total respondents to detect a moderate difference (f = .25) between all four strata. As analysis is exploratory, we do not intend to correct for multiple hypothesis testing.   1. Expert strata analysis: 2. The order of predicted replication rates will be: 3. Novices/Non-experts (Should be optimistic since and less attuned to the “replicability crisis” across scientific disciplines) 4. Originators (if available- should be optimistic due to their investment in these results, but more realistic than novices) 5. Independent Experts (Should be less biased due to independence from findings) 6. Replicators (if available- theoretically well attuned to flawed research design and practices) 7. The order of forecast skill will be: 8. Independent Experts (should have sufficient expertise and less biased by own work) 9. Originators (if available- should have sufficient expertise, but more myside bias) 10. Replicators (if available- assumes lab skills are higher than knowledge for this group) 11. Novices/Non-experts (assuming expertise and forecast skill are related, they have the least expertise) 12. The order of variability in forecasts will be: 13. Novices/Non-experts (assuming expertise and forecast skill are related, there should be more variability for those with the least knowledge) 14. Independent Experts 15. Replicators (if available- assumes replicators are well attuned to good and bad study design and difficulty of carrying out certain studies) 16. Originators (if available- assuming expertise and forecast skill are related, there should be less variability in recognizing real empirical relationships and flawed study design by those who have devoted their lives to studying these topics) 17. Expertise will have an inverse U-shaped (∩) relationship with forecasting success. People with low expertise will perform poorly due to inadequate information, and people with high expertise will perform poorly due to maladaptive beliefs (e.g. confirmation bias). The correlation between perceived expertise and Brier score will be ranked as follows:      1. Originators (if available- should perform when they claim higher expertise; have motivation to honestly claim high expertise for some, but not all topics) 2. Independent Experts (may be less discriminating in expertise ratings than originators since they don’t have personal relationships with any of the studies) 3. Replicators (if available) 4. Novices/Non-experts (should have consistently low expertise ratings) 5. Predictors of Forecast Skill: We will test the relationship between each demographic and scale variables and Brier Skill Score, secondarily looking at components of calibration and discrimination. The individual differences should influence the forecasts in the following order (from most to least influential). 6. More extreme updaters: Those who update more extremely relative their will have more accurate forecasts^[[5]](#footnote-5)^. 7. Pace of progress: Those who believe medical technology should progress quickly (slowly) will have more optimistic (pessimistic) forecasts. 8. Evidence reliance: 9. Those who rate the methodology of the replication attempt as important will be pessimistic. 10. Those who cite specific trial outcomes as evidence will be worse forecasters, and those who cite treatment or disease type (base rates) will be better forecasters. 11. Expertise: Those will high (self-reported and actual) expertise will be more accurate; actual expertise (H- & M-indices) will be more predictive of forecasting skill. 12. Confidence will be weakly correlated with forecasting skill. We expect a hard-easy effect where forecasters are overconfident on hard items and underconfident on easy items. 13. Demographics     1. We will also test methods of identifying forecasting skill early (prior to target event realization) the relationship between individual forecaster’s Brier scores and their average squared distance to the median compared to other baselines (mean, expectation due to chance, expectation due to base rates if available) - we hypothesize that this will lead to a strong relationship with forecast skill. 14. Aggregation of Forecasts 1: We will test whether different aggregation approaches give better forecast performance (i.e. lower Brier scores). First, to determine the relative value of using combined forecasts to make decisions, we will construct a curve of showing the relationship between Brier scores and number of aggregated forecasts. Specifically, the curve will reflect n=0 aggregation (i.e. average Brier scores of individual forecasters); n=1 (i.e. average Brier score when two forecasters forecasts are randomly aggregated); n=4 (i.e. average Brier score when 5 randomly selected forecasts are aggregated); and n=9 (i.e. average Brier score when 10 randomly selected forecasts are aggregated). We will also use transformations to make predictions more extreme.[16,17] 15. Predictors and Aggregation: Using individual differences and demographic variables that show low skill identified in step 1, we will test the competitiveness of aggregated low skill forecasters with the individual scores of high skill forecasters. For instance, suppose we find a relationship between high M-index and high forecast skill. We will then test whether, if we combine forecasts from 2, 3, 5 and 10 low M-index forecasters, on average the forecast outperforms the average forecast of high M-index forecasters.   After we have completed forecast scoring, we will also rank all individual forecasters by their Brier skill scores, and randomly select individuals within tiers of upper, middle, and lower thirds. We will test whether combined forecasts of 2, 3, 5 and 10 “low skill” forecasters can, on average, beat the forecast of randomly selected individuals from each skill tier. Brier scores will be used; as well, they will be decomposed into discrimination and calibration. |

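### Novices forecast one set of three studies and half the experts forecast another, yet the secondary expert–novice contrasts on study-level forecasts are not limited to shared studies or adjusted for study

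*Protocol*

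**What the plan says.** The Survey Versions list in the Protocol Appendix has an expert form with studies 15, 21 and 44, and "Expert survey 2" with "Studies, 19, 29, & 39". Each is repeated as an incentive pilot with the same studies. The only novice form is "Novice survey 1", with studies 15, 21 and 44; no second novice form is listed.

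The SAMPLING section agrees. It states "We will split the trial sample into two surveys to minimize the number of trials for which participants only have general expertise", and the target is "50X2=100 independent experts + 50 novices", which is 50 experts per survey and one group of 50 novices. The expected minimum is 30 per expert survey and 30 novices. INTERVIEW AND DATA COLLECTION lists "2 binary: Significant difference and direction on 3 replication studies". One sentence in SAMPLING conflicts with this: in stage 1, "participants will forecast all of the first six (all based on mouse models) studies".

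SECONDARY ANALYSIS ON FORECAST SKILL then sets out expected orderings of the strata on predicted replication rates, on skill ("The order of forecast skill will be"), on variability of forecasts, and on the correlation between perceived expertise and Brier score. It gives a sample size for experts against novices. It does not say which experts enter, and it has no term for study or survey.

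**The concern.** A person's study-level Brier score rests on three studies, so each outcome moves a third of the score on that question. Half the planned expert scores come from studies that no novice saw. If one set happens to contain more successful replications, experts and novices of identical skill will show different mean scores, and the difference will be read as an effect of expertise.

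Predicted probabilities do not depend on outcomes, but they can depend on content. If the survey 2 studies simply look more or less replicable, the experts' mean study-level forecast and its spread will shift against the novices'.

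The same pooling arises among experts alone. Predictor analyses, skill thirds and expert prizes would partly reflect which survey a person received.

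**Working it through.** **The plan's own figure.** The protocol gives 34 per group for experts against novices (d = .5, power .80, alpha .05). A two-sample t test needs 64 per group two-sided, or 51 one-sided. A one-sample two-sided t test gives 33.4, hence 34, so the figure fits only a comparison with a constant. That is a separate error, and the present point does not rest on it.

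**Size of the spurious difference.** Let r1 and r2 be the numbers of positive outcomes (out of three) in surveys 1 and 2 on one question, and f a common forecast.

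- Mean Brier score on a survey with r positives: (r/3)(1 − f)² + (1 − r/3)f² = f² + (r/3)(1 − 2f).
- Novices (survey 1): f² + (r1/3)(1 − 2f).
- Experts, half on each survey: f² + ½(r1/3 + r2/3)(1 − 2f).
- Expert minus novice: ½ × (r2 − r1)/3 × (1 − 2f).

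The difference is zero if r1 = r2 or f = .5. For a one-study gap its absolute size is:

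- f = .60: ½ × 1/3 × .20 = .033
- f = .65: ½ × 1/3 × .30 = .050
- f = .70: ½ × 1/3 × .40 = .067
- f = .80: ½ × 1/3 × .60 = .100

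A two-study gap doubles these.

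**How often the counts differ.** If each study replicates independently with probability p, P(r1 ≠ r2) = 1 − Σ q_k², where q_k is the binomial(3, p) probability of k successes.

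- p = .05: 1 − (.857² + .135² + .007²) = .25
- p = .10: 1 − (.729² + .243² + .027² + .001²) = .41
- p = .30: 1 − (.343² + .441² + .189² + .027²) = .65
- p = .50: 1 − (2 × .125² + 2 × .375²) = .69

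**False-positive rate.** Simulation with identical skill in both groups, mean forecast .65, SD .20, and a Welch t test on individual mean Brier scores at nominal 5%. The forecast distribution and the replication probabilities are assumptions; the group sizes are the protocol's.

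| Scenario (100 v 50) | All experts pooled | Survey 1 experts only |
|---|---|---|
| p = .05 to .10 | about .18 to .27 | about .05 |
| p = .3 to .5 | .42 to .54 | about .05 |
| one success in one survey, none in the other | about .50 to .58 | about .05 |
| equal success counts | about .05 | about .05 |
| mean forecast .50 | no inflation | about .05 |

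At the minimum sizes (60 v 30) and p = .3 to .5, pooling gives 33–43%. The rates move with the forecast distribution. Other assumptions gave as little as 12% at p = .05 to .10 and 22% for a single discordant study. A mean forecast of .70 gave .51 when only survey 2 had a success and .74 when only survey 1 did.

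**Predicted probabilities.** If survey 2 studies look 10 points more replicable (an assumption), the pooled expert mean moves by ½ × 10 = 5 points with no difference in expertise.

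**Power after restriction** (two-sided, d = .5): 50 v 50 gives .70 (detectable d = .57 at 80% power), and 30 v 30 gives .48 (detectable d = .74). Pooling would give .82 at 100 v 50 and .60 at 60 v 30, but across different study sets.

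**The case against.** - **Outcomes varied little.** Footnote 4 says replication results varied too little for some analyses to be run. This stands in part: with equal success counts the outcome-driven bias is nil. But the footnote gives no split by survey or by question, it reports something known only afterwards, and it does not cover shifts in forecasts due to study content.
- **Not every contrast is exposed.** This stands. The forecasts of overall replication rates are not tied to a survey's studies. The protocol does not say which measure its ordering of predicted replication rates uses, so only study-level probabilities are at issue. A reader might infer that the whole strata analysis is contaminated; the documents do not support that.
- **Prizes are awarded within stratum.** This stands. All novices answer one form and never compete with experts, so only ranking among experts across the two surveys is affected.
- **The Brier Skill Score might absorb the difference.** Not reliably: depending on the reference chosen, rejection ran from about 6% to 55%, and no survey-specific reference is specified.
- **All participants forecast six studies.** One sentence says so, and on that reading there is no confounding. The per-person count of three studies, the split into two surveys and the survey map all contradict it; the passages should be reconciled.
- **The detail may sit in an SAP.** Possible. The protocol does not say outright that all experts are pooled. But it sets both the allocation of studies and the contrasts, and leaves them unconnected.
- **The analysis is exploratory.** This bears on severity. The label does not remove a confounder.

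**Conclusion.** The concern holds for secondary, study-level expert–novice contrasts. As written, the plan lets study set stand in for expertise. The Brier bias is ½ × (r2 − r1)/3 × (1 − 2f): .05 for a one-study gap at a mean forecast of 65%, and zero with equal counts or a 50% mean forecast. The protocol itself expects forecasts to run above the observed replication rate, so a mean of exactly 50% should not be relied on.

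The rejection rates of 42–54% are tempting as a headline, but they depend on assumed replication probabilities of .3–.5. At .05–.10, closer to what footnote 4 may imply, the rate is about 18–27%. A reader might also infer that the completed comparison was in fact biased. The documents cannot show that, because outcomes by survey are not given, and the realised bias may be small or nil.

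The primary objectives and primary analysis, expert accuracy against a constant or base rate, do not depend on the novice contrast. This should be fixed, but it does not undermine the primary conclusions.

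**What to change.** State that every study-level expert–novice contrast uses survey 1 experts against novices (studies 15, 21 and 44). A model of per-study scores with a fixed effect for study would serve equally: survey 2 experts then add nothing to the group contrast, since no novice saw their studies. Describe survey 2 experts separately. Include survey version in the predictor analyses. Rank experts within survey version, including for skill tiers and expert prizes. Leave the overall replication-rate contrasts on the full sample. Correct the sentence saying each participant forecasts all six studies, or the passages that contradict it.

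This is a change of analysis wording and needs no new data. The cost is precision: the contrast falls from 100 v 50 to 50 v 50 (power .70 for d = .5), or from 60 v 30 to 30 v 30 (power .48), and the protocol should say so. Its 34-per-group statement should not be used to defend either size.

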**Sample Information Sheet**

| **Coadministration of a tumor-penetrating peptide enhances the efficacy of cancer drugs**  Sugahara, K. N., Teesalu, T., Karmali, P. P., … Ruoslahti, E.[18]  **Link to original paper:** <http://www.ncbi.nlm.nih.gov/pmc/articles/PMC2881692/> **Link to replication plan:** <http://elifesciences.org/content/4/e06959>  In the above study, the authors showed that a tumor-penetrating peptide, iRGD, when given to mice with orthotopic human prostate tumors, resulted in significantly greater anti-tumor activity for the small molecule drug, doxorubicin, as compared with animals given doxorubicin without the tumor-penetrating peptide (see arrows). The following 3 questions refer to the replication of this effect.  [figure not shown] | | |
| --- | --- | --- |
|  | **Subjective Probability** (%) | **Confidence** (%) |
| 4. *Based on the claims of this paper*, how likely is it that the replication will also be **significant (at p ≤ .05)**? |  |  |
| 5. *Based on the claims of this paper*, how likely is it that the **effect size** of the replication will be **as large or larger than the original effect size**? |  |  |

**Original Studies**[18–23] **Undergoing Replication**

|  |  |  |  |  |
| --- | --- | --- | --- | --- |
| Study # | First Author | Title | Journal | Year |
| 15 | Sugahara | Coadministration of a tumor-penetrating peptide enhances the efficacy of cancer drugs | Science | 2010 |
| 21 | Sirota | Discovery and preclinical validation of drug indications using compendia of public gene expression data | Science | 2011 |
| 44 | Berger | Melanoma genome sequencing reveals frequent PREX2 mutations | Nature | 2012 |
| 19 | Delmore | BET bromodomain inhibition as a therapeutic strategy to target c-Myc | Cell | 2011 |
| 29 | Dawson | Inhibition of BET recruitement to chromatin as an effective treatment for MLL-fusion leukaemia | Nature | 2011 |
| 39 | Willingham | The CD47-signal regulatory preotein alpha (SIRPa) interaction is a therapeutic target for human solid tumors | PNAS | 2012 |

